## Sample size

Results from previous randomized controlled trials suggest that group prenatal reduces likelihood of delivering a preterm or small for gestational age baby by 33–34% [18, 21]. Based on these findings and the national preterm birth rate of 9.6% [4], we need a minimum of 1,768 study participants with one-third (*n* = 884) receiving group prenatal care to have power of .80 to detect differences at alpha = 0.05 with a one-tailed test. With a potential 10% drop out rate due to miscarriage, pregnancy complications and changes in life circumstances (e.g., geographic move), we will recruit 1,000 women, expecting to follow more than 900 of them through one-year postpartum. We will compare primary maternal health and birth outcomes for these women with a 2–1 matched cohort of 2,000 patients receiving individual care. Therefore, the total study sample of women receiving both group and individual prenatal care will include a total of 3,000 women.

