To collect organizational data, all clinic staff involved in implementing *Expect With Me* were asked to participate in the process evaluation. To collect extensive data on individual-level outcomes, patients who participate in *Expect With Me* are required to enroll in the evaluation study. We aim to follow more than 1,000 pregnant women through one-year postpartum. Inclusion criteria for patients are as follows: less than 24 weeks pregnant; no severe medical problem requiring individual care only, as determined by the clinical practice; ability to speak English or Spanish; and willingness to participate in the study. Staff at each clinical site explain the study to eligible participants, answer questions, and obtain informed consent. A two-to-one matched cohort of women receiving standard individual care at each clinical site will provide the comparison for the outcome evaluation (two individual care patients for each group care patient). The matched cohort inclusion criteria mirror the study inclusion criteria (e.g., receiving prenatal care at the same clinical practice, entered prenatal care <24 weeks gestation, not transferred out to a high-risk clinic, fluent in English or Spanish, entered prenatal care during the study timeframe). All procedures have been approved by the Yale University Institutional Review Board and Institutional Review Boards at each study site.

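### The stated minimum sample size contradicts itself: 884 is half of 1,768, not one-third, and 1,768 women split 1:2 fall short of the stated 80% power

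*Protocol article*

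**What the plan says.** The Sample size section takes its effect from earlier randomized trials, in which group prenatal care "reduces likelihood of delivering a preterm or small for gestational age baby by 33–34" per cent, and its comparison rate from "the national preterm birth rate of 9.6" per cent. From these it concludes that "we need a minimum of 1,768 study participants with one-third", given as n = 884, in group care are enough "to have power of .80 to detect differences at alpha = 0.05 with a one-tailed test".

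The same section then allows for 10% dropout, recruits 1,000 group-care women, expects to follow more than 900 of them for a year, and adds a matched cohort of 2,000 individual-care women, 3,000 in all. The 2:1 ratio and the 1,000 and 2,000 also stand in the Abstract. The ratio is repeated under Organizations and study population, where the follow-up target reads differently: "We aim to follow more than 1,000 pregnant women through one-year postpartum".

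**The concern.** The sentence gives a total, a fraction and a group size, and any two of them contradict the third. A reader cannot tell whether the minimum is 1,768 or 2,652 women. Nor can the reader tell whether the calculation behind it was 1:1 or 1:2, or whether it really used the one-tailed test that is named.

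This is the article's only statement of the minimum sample and of sidedness. Sidedness matters: at 884 + 1,768 and a 33% reduction, power is 0.88 one-tailed but 0.80 two-sided. If matching or recruitment fell short and someone took 1,768 with one-third in group care as the floor, the study would miss its stated power on the standard test.

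**Working it through.** **Inputs, all from the Sample size section.** Individual-care rate p_c = 0.096. Reduction 33–34%, read as a relative risk reduction, so group-care rate p_g = 0.096 × 0.67 = 0.06432 down to 0.096 × 0.66 = 0.06336. Alpha 0.05, power 0.80. Individual-care women per group-care woman: k = 2.

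**Step 1: the fractions (no model needed).**
- 884 / 1,768 = 0.500
- 1,768 / 3 = 589
- 884 × 3 = 2,652, and 2,652 − 884 = 1,768

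**Step 2: can the plan's figure be reproduced as stated (1:2, one-tailed)?** Pooled-variance formula for two proportions, with p̄ = (p_g + k·p_c)/(1 + k):

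n_g = [z_α √((1 + 1/k) p̄(1 − p̄)) + z_β √(p_g(1 − p_g) + p_c(1 − p_c)/k)]² / (p_c − p_g)²

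- 33%: p̄ = 0.08544 and the difference is 0.03168. The two terms are 0.5631 and 0.2709, so n_g = (0.8340 / 0.03168)² = 693.03. That is 694 group-care and 1,387 individual-care women, about 2,082 in total (694 × 3).
- 34%: n_g rounds up to 650, with 1,300 individual-care women, 1,950 in total.

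Neither 1,768 as a total nor 884 in group care appears. Against these totals, 1,768 is short by 182 to 314 women.

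**Step 3: power of 1,768 women split 1:2 (589 + 1,179).**

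Power = Φ[(p_c − p_g − z_α·SE₀) / SE₁], with SE₀ pooled and SE₁ unpooled.

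- 33%, one-tailed: (0.03168 − 1.645 × 0.01411) / 0.01326 = 0.640, power 0.739.
- 34%, one-tailed: (0.03264 − 1.645 × 0.01408) / 0.01320 = 0.718, power 0.764.
- Two-sided: 0.620 and 0.649.

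Exact enumeration of the pooled test gives 0.743–0.768 one-tailed, so the shortfall is not an artefact of the normal approximation.

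**Step 4: which calculations return the printed numbers?**

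| Reading | Required for 80% power | Power at the printed numbers |
|---|---|---|
| 1:2, two-sided, 33% | 883.9, so 884 + 1,768 = 2,652 | 0.800 (884 + 1,768) |
| 1:1, one-tailed, 33% / 33.5% / 34% | 908 / 879 / 851 per arm | 0.791 / 0.802 / 0.813 (884 + 884) |

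For the first row, the terms are 0.6710 and 0.2709, and (0.9419 / 0.03168)² = 883.9.

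**Step 5: the planned sample after 10% loss in both groups (900 + 1,800).** One-tailed power is 0.886 (33%) to 0.903 (34%); two-sided power is 0.807 to 0.833. Also, 884 / 0.90 = 983, consistent with recruiting 1,000.

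**The case against.** The strongest reply is that nothing operational depends on the sentence. The article does not make 1,768 a fallback or a stopping target. The working plan of 1,000 + 2,000 is stated consistently and has adequate power on either sidedness. That stands, and it limits the point to a reporting correction.

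A second reply is that the power shortfall depends on the formula. With unpooled variance, 589 + 1,179 reaches 0.772 to 0.796 one-tailed, so at the most favourable 34% reduction it is practically 0.80. This stands too, but group care would then number 589, and the printed 884 is still unexplained.

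A reader might go further and infer that 1,768 is simply the individual-care arm, that the test was really two-sided, and that the minimum is therefore understated by 884 women. The exact match in Step 4 makes this tempting, and it respects both the one-third and the 2:1 design. The document does not establish it. It says one-tailed, and it calls 1,768 the study participants. The 1:1, one-tailed reading keeps both of those statements and brackets 0.80 across the document's own 33–34% range, though it contradicts the one-third and the 2:1 matching. Under the test that the article names, the shortfall at 1:2 is about 182–314 women, not 884.

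On follow-up, an aim of more than 1,000 and an expectation of more than 900 after attrition can be seen as two different kinds of statement. With 1,000 recruited and losses expected, however, the aim cannot be met as worded. This is minor and does not bear on the power calculation.

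**Conclusion.** The point holds as an error in the stated justification. The conflict between 884, one-third and 1,768 is plain arithmetic and rests on no assumption. That 1,768 women at 1:2 give about 0.74–0.76 rather than 0.80 rests on the pooled test, the stated one-tailed 0.05, and the 33–34% read as a relative risk reduction from 9.6%.

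It would be wrong to conclude that the study is underpowered. On the same assumptions the planned sample keeps at least 0.80 after 10% loss, one-tailed or two-sided. Two limits apply to that reassurance. The figures ignore matching and clustering by site or group. And if the reduction were read as one in odds, 900 + 1,800 would give 0.84–0.86 one-tailed but 0.74–0.77 two-sided, which is one more reason to state the sidedness and the effect measure clearly.

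**What to change.** Check the original calculation, then restate total, split, sidedness and power in one sentence:

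- If it was 1:2 and two-sided at a 33% reduction: 884 group-care and 1,768 individual-care women, 2,652 in total, for 80% power at two-sided 0.05 (0.88 one-tailed).
- If the 1:2, one-tailed test is kept: about 650–694 group-care and 1,300–1,387 individual-care women for 80% power, naming the reduction used.

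If the source turns out to be a 1:1 calculation, it does not describe the matched design and should be replaced by one of these two. Also align the follow-up target under Organizations and study population with the Sample size section: recruit 1,000, follow more than 900.

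The cost is wording only. The planned 1,000 + 2,000 already exceeds each of these minima and need not change.

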## Methods/Design

*Expect With Me* is being evaluated via a multisite, longitudinal matched-cohort study, in which data are collected in a real-world settings at the patient and organizational levels. For national scale-up and sustainability, it is essential that the program not only be effective for patients but that the implementation strategy fits with the context of health clinics providing prenatal care [52]. A rigorous multi-method evaluation is being conducted to examine the impact of *Expect With Me* on maternal health and birth outcomes and identify and address barriers to national scalability. Cost analyses are also planned.

The study includes a rigorous process and outcome evaluation. Birth outcomes are the primary study outcomes (e.g., preterm birth, birthweight, neonatal intensive care unit admission/duration). Maternal psychosocial, health behaviors, and health outcomes (e.g., depression, breastfeeding, postpartum weight loss) are secondary outcomes.

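### The only significance level stated is an unexplained one-tailed 5% test, which the planned sample does not need, in a sample-size sentence whose figures contradict each other

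*Protocol article*

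**What the plan says.** The Sample size section takes its effect from earlier randomised trials, in which "group prenatal reduces likelihood of delivering a preterm or small for gestational age baby by 33–34" per cent, and its comparison rate from "the national preterm birth rate of 9.6" per cent. It then says "we need a minimum of 1,768 study participants with one-third" of them, given as 884, in group care, "to have power of .80 to detect differences at alpha = 0.05 with a one-tailed test". It allows for 10% dropout, recruits 1,000 group-care women, expects to follow more than 900, and compares them with 2,000 matched individual-care women.

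Under Organizations and study population the matching is "two individual care patients for each group care patient". The Methods/Design section puts the aim without a direction: "A rigorous multi-method evaluation is being conducted to examine the impact of" the model on maternal health and birth outcomes. The Analyses section names the regression models and the treatment main effect, but gives no alpha and no sidedness.

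**The concern.** A one-tailed 5% test has the same critical value as a two-sided 10% test. It suits a setting where an effect in the unfavourable direction would be of no interest, and that is hard to argue here. Women are not randomised. The Analyses section itself describes propensity matching as dealing with observable differences, so residual selection could push the estimate either way. The team that developed the model is evaluating it, and the Discussion says the findings will shape its dissemination. A higher preterm or neonatal intensive care rate under group care would be an important finding.

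If the outcome models use the threshold in the sample-size sentence, a favourable result with a two-sided p between 0.05 and 0.10 would count as positive, and an unfavourable result of any size could not be declared. Separately, the sentence carrying the threshold gives numbers that cannot all be right, so a reader cannot tell which test the study was sized for.

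**Working it through.** **Inputs (Sample size section, except the ratio).** Individual-care rate p1 = 0.096. Reduction 33–34%, read as a risk ratio (RR) of 0.67 to 0.66, so the group-care rate p2 = 0.096 × 0.67 = 0.0643 (or 0.096 × 0.66 = 0.0634). Power 0.80. Ratio k = 2 individual-care women per group-care woman (Organizations and study population). Normal quantiles: 1.645 for one-tailed 5%, 1.960 for two-sided 5%, 0.842 for 80% power.

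**Formula (pooled two-proportion test, no continuity correction).** With p̄ = (p2 + k·p1)/(1 + k),

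n(group) = [ zα·√((1 + 1/k)·p̄(1 − p̄)) + zβ·√(p2(1 − p2) + p1(1 − p1)/k) ]² / (p1 − p2)²

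**Step 1: the calculation as described (one-tailed, 2:1).**
- RR 0.67: p̄ = 0.0854 and n = [(0.5631 + 0.2709)/0.03168]² ≈ 693.0, so 694 + 1,388 = 2,082.
- RR 0.66: 650 + 1,300 = 1,950.
- Neither gives 1,768 in total with 884 in group care. An unpooled variance at RR 0.66 gives a total near 1,789, but then the group arm is about 596, not 884.

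**Step 2: internal arithmetic.** 884/1,768 = 0.50, not one-third. One-third of 1,768 is 589. 884 is one-third of 2,652.

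**Step 3: which calculations give 884 and 1,768?** Two do.
- Two-sided 5%, 2:1, RR 0.67: n = [(0.6710 + 0.2709)/0.03168]² ≈ 883.9. That is 884 group + 1,768 individual = 2,652, with 1,768 as the individual-care arm.
- One-tailed 5%, 1:1, RR 0.666: n ≈ 883.8, so 884 per arm and 1,768 in total. This contradicts both the one-third share and the 2:1 design.

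**Step 4: power at the planned sizes, 2:1, independent observations.** Power = Φ{ [(p1 − p2) − zα·s0]/s1 }, where s0 and s1 are the pooled and unpooled standard errors. For 900 + 1,800 at RR 0.67, s0 = 0.01141 and s1 = 0.01073. Two-sided, (0.03168 − 1.960 × 0.01141)/0.01073 ≈ 0.868, and Φ = 0.807.

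| Group + individual | Two-sided, RR 0.67 | Two-sided, RR 0.66 | One-tailed, RR 0.67 |
|---|---|---|---|
| 589 + 1,179 (1,768 split 1:2) | 0.62 | 0.65 | 0.74 |
| 884 + 1,768 | 0.80 | 0.83 | 0.88 |
| 900 + 1,800 | 0.81 | 0.83 | 0.89 |
| 1,000 + 2,000 | 0.85 | 0.87 | 0.91 |

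**Step 5: sensitivity.**
- If 33–34% is a reduction in odds, p2 is 0.0664 to 0.0655, and two-sided power is 0.745–0.773 at 900 + 1,800 and 0.79–0.82 at 1,000 + 2,000.
- The article gives no intracluster correlation. Assuming 0.01 and groups of 10 (the article's range is 8–12), the design effect in the group-care arm is 1 + 9 × 0.01 = 1.09, and 900/1.09 ≈ 826 effective women. Two-sided power at RR 0.67 is then about 0.78.

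**Step 6: error rates.** The probability of a false positive in the favourable direction is 0.05 for a one-tailed 5% test and 0.05/2 = 0.025 for a two-sided 5% test.

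**The case against.** The strongest objection is that sidedness appears only in a sample-size sentence, which is a planning assumption and not a decision rule. A reader might infer that the study will declare success at a two-sided p below 0.10 and can never report harm. The article does not say so. The Analyses section sets no threshold, an analysis plan that is not shown may set one, and scale-up is also tied to process, cost and qualitative evidence. This stands, and the error-rate consequences are therefore conditional.

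A reader might also infer from the exact match in the two-sided 2:1 calculation that one-tailed is simply a slip. The documents do not settle this, because a one-tailed 1:1 calculation at RR 0.666, within the stated 33–34%, gives the same two numbers.

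A third objection is that the earlier randomised trials justify a direction. They support expecting benefit, but they do not make an adverse estimate uninteresting in a non-randomised comparison, and the article offers no such argument.

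Finally, the margin over 80% is thin. That stands too: 0.807 at 900 + 1,800 depends on reading the reduction as one of risk and on ignoring clustering.

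**Conclusion.** The point holds in conditional form. The article's one stated significance level is one-tailed 5%, without justification. If it carries over to the outcome models, the favourable-direction error doubles from 2.5% to 5% and there is no rejection region for harm. The sample does not require it: two-sided power is 0.80 to 0.85 at RR 0.67 across 884 + 1,768 to 1,000 + 2,000, given a risk reduction from 9.6% to 6.43% and independent observations. Unconditionally, the sample-size sentence is wrong as printed. 884 is not one-third of 1,768, and a one-tailed 2:1 calculation with the formula above needs about 1,950 to 2,080 women.

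**What to change.** State two-sided 5% tests with 95% confidence intervals for the primary between-arm comparisons. Rewrite the sample-size sentence to say that 884 group-care and 1,768 individual-care women, 2,652 in total, give 80% power at two-sided 5% for a one-third-lower risk (RR 0.67 against 9.6%), and that this assumes a risk reduction and no clustering.

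Replacing one-tailed with two-sided alone is not enough. It would leave 1,768 participants with one-third in group care, a 589 + 1,179 split with two-sided power of only 0.62 to 0.65.

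The cost is a wording change. The planned 1,000 + 2,000 stays as it is. Stated power at 900 + 1,800 falls from about 0.89 (one-tailed) to about 0.81, and could be somewhat below 0.80 on an odds-ratio reading or with clustering by group.

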## Trial status

This study has been registered on ClinicalTrials.gov as NCT02169024. All data collection will be completed by December 2017.

## Discussion

Combined maternal and newborn care is the most common and expensive category of hospital care for all payers costing $52 billion for Medicaid and $40 billion for private insurers, annually [69]. High rates of preterm birth and low birth weight are important drivers of these costs. Moreover, gross disparities in these and other reproductive health outcomes are grounds for “evidence-based outrage” [70]. National initiatives to tackle disparities and rising rates of maternal morbidity and mortality [71–73] make a renewed focus on prenatal care access, structure, content and quality not only timely, but essential [74].

Group prenatal care has shown promise to reduce rates of adverse birth outcomes, particularly among African American women, but widespread dissemination of this important health care innovation has yet to realized. This paper describes the development and methods that are being used to comprehensively evaluate *Expect With Me*, an innovative model of group prenatal care with an integrated information technology platform designed to be scalable nationally.

Researchers, clinicians, health care administrators, insurers, and policy-makers will have significant interest in the results of this study if we can demonstrate that bundling prevention and care services into a *high-touch, high-tech* group prenatal care model (i.e., *Expect With Me*) meets the “triple aim” for maternity care: better healthcare quality, improved outcomes, and lower health care costs. Most importantly, families will avoid the emotional toll and lifetime health and education costs associated with adverse birth outcomes. Findings from this study will be used to formulate recommendations to optimize the dissemination and effectiveness of this model of group prenatal care.
